## Abstract

**Background:**

Immunotherapy is currently applied in the first-line treatment regimens for numerous advanced cancers, especially advanced lung cancer. Immune-related adverse events (irAEs) resulting from immunotherapy can vary in severity and cause a substantial symptom burden to patients. However, there are limited data on symptom burden in patients with advanced lung cancer following immunotherapy. To address this deficit, this study aims to provide insight into the symptom burden and severity through patient-reported outcome measurements and conduct an analysis of temporal trends and clinical consequences of symptom burden in patients with advanced lung cancer receiving combination immunotherapy.

**Methods:**

We will prospectively recruit 168 eligible patients from 14 hospitals in China. Eligible patients will be aged ≥ 18 years, pathologically diagnosed with locally advanced or stage IV primary lung cancer without surgical indications, and agreed to receive immunotherapy in combination with other therapies. The primary outcome of this study is the symptom burden of patients during the immunotherapy course. Longitudinal symptom data will be collected using the MD Anderson Symptom Inventory–Lung Cancer module (MDASI-LC) and the symptomatic irAEs scale at baseline (once before treatment) and weekly after treatment, until 1 month after the last treatment cycle has been completed. The trajectory of symptom burden following combination immunotherapy will be depicted, and by linking it to clinical outcomes (the secondary outcome and exploratory outcome of this study), the consequence of symptom burden in patients with advanced lung cancer receiving combination immunotherapy will be examined further.

**Discussion:**

This study intends to establish longitudinal symptom trajectories in patients with lung cancer receiving immunotherapy, and explore its association with clinical outcomes. These findings may serve as an important reference for clinicians in the symptomatic management of patients with lung cancer receiving immunotherapy.

**Trial registration number:**

ChiCTR2200061540. Registered on June 28, 2022.

## Background

Lung cancer is the second most common malignancy and most lethal cancer worldwide, with highest morbidity and mortality rates in China [1]. Many patients with lung cancer are already in the advanced stages at initial clinical diagnosis, thereby having poor prognosis and a relatively short overall survival. Cancer immunotherapy, especially immune checkpoint inhibitors (ICIs), is an emerging therapeutic strategy, and combination therapy with traditional chemotherapy or radiation therapy has played an important role in the treatment of advanced lung cancer. It has markedly improved the survival of some patients, and a significant fraction of patients can achieve long-term survival of ≥ 5 years [2]. Therefore, regarding ICIs, the quality of life of patients with long-term survival is extremely important. Combination immunotherapy for lung cancer is associated with significant treatment-related symptoms [3]. Therein, irAEs following ICIs generally have a long duration and broad spectrum [4] and can cause physical and psychosocial burdens on patients, thereby negatively affecting quality of life and compliance with therapy.

Symptoms in patients with lung cancer receiving immunotherapy are traditionally assessed by the medical staff rather than self-reports from patients [5, 6]. PRO (patient-reported outcome) is a non-traditional clinical indicator of capturing patient symptoms, functional outcomes, or health-related quality of life directly from the patients’ perspective without interpretation from others [7, 8]. Screening of PRO followed by tailored interventions can achieve better clinical outcomes [9]. In patients with advanced lung cancer, much attention has been focused on tracking adverse event symptoms induced by chemotherapy, which showed significant survival benefits when combined with threshold-driven alter and response [10, 11].

However, the longitudinal symptom trajectories after immunotherapy treatment in patients with advanced lung cancer have not been addressed yet. Particularly, immunotherapy is a new treatment paradigm and can lead to complex irAEs with relative specificity. Addition of PROs to traditionally collected outcomes can provide a comprehensive overview of patient experience during and after treatment [9]. It is, therefore, necessary to track the symptom trajectories after immunotherapy treatment directly from patient self-reports. Moreover, the current understanding of the association between patient-reported symptoms following immunotherapy and clinical outcomes is limited, and only a few indicators (e.g., overall survival and progression-free survival) have been reported [12]. The connection between symptom burden and clinical outcomes, including the completion rate of immunotherapy, timeliness of treatment, complication rate, and unplanned clinic rate may be critical for clinicians to manage adverse events.

However, some questions and challenges remain unaddressed for symptom assessments in patients with lung cancer receiving immunotherapy. First, immunotherapy-specific items are noticeably missing in all lung cancer modules of commonly used PRO measures (PROM). For instance, although the MDASI-LC is widely used in the medical community at present, it is primarily designed for patients receiving chemoradiation [13], and is applied in the realm of radiotherapy [14] and operation [15]. Some frequently reported irAEs symptoms, such as diarrhea, rash, and fever, have not been included, limiting its application in detecting patients’ experience during immunotherapy. Therefore, updating those measures by introducing immune-specific PRO symptom clusters for better application in both clinical practice and research is essential. Second, optimal symptom monitoring time points for immunotherapy remain undefined, while irAEs are characterized by recurrent, long-standing, and dynamic changes as well as sudden and dramatic adverse prognostic factors [16]. The time points of PRO data collected during hospitalization and after discharge should be combined with the above characteristics to avoid the omission of real symptoms and artifacts and reflect the rules of immunotherapy, with the consideration of system burden-induced by frequent assessment schedule. Third, warning signals of irAEs for medical intervention require more evidence for support. In clinical practice, irAEs with complexity and relative specificity are difficult to be precisely managed. Thorough insight into the connection between irAEs and key clinical outcomes will help in clinical decision-making and management.

Thus, using a multicenter longitudinal cohort design, this study aims to leverage PRO data to establish temporal trends in the symptom burden of patients with advanced lung cancer receiving combination immunotherapy, and examine its association with clinical outcomes. These findings are necessary for clinical decision-making and supportive care for patients with advanced lung cancer receiving immunotherapy.

## Methods/Design

### Study design

This is a multicenter observational prospective cohort study. The flowchart of the study is shown in Fig. 1.

**Fig. 1 Fig1:**
[figure not shown]
The flow chart of this study

### Study setting

The study will be initiated by Sichuan Cancer Hospital and conducted in 14 hospitals in China, namely, Sichuan Cancer Hospital, Third People’s Hospital of Chengdu, Seventh People’s Hospital of Chengdu, Western Theater General Hospital, Sichuan Provincial People’s Hospital, First Affiliated Hospital of Chengdu Medical College, Chengdu Second People’s Hospital, Mianyang Central Hospital, Nanchong Central Hospital, West China Hospital of Sichuan University, Deyang people’s Hospital, Suining people’s Hospital, Dujiangyan people’s Hospital and Chengdu Fifth People’s hospital. Each patient will be followed up from before the treatment to 1 month after the completion of the last cycle of immunotherapy. This study has been ongoing since June 2022 and is currently planned to be continued until December 2024.

### Study population

The patients included in the study are those with a diagnosis of advanced primary lung cancer and prescribed combination immunotherapy as first-line treatment. The inclusion and exclusion criteria for this study are listed in Table 1.

**Table 1 Tab1:** The inclusion and exclusion criteria for this study

Inclusion criteria	Exclusion criteria
✓ Pathologically confirmed advanced or stage IV primary lung cancer who had no surgical indicators.	× Age < 18 years old at the time of informed consent.
✓ Scheduled to receive combination immunotherapy as the first-line treatment.	× Cognitive impairment or inability to understand the research content.

### Withdrawal criteria

Participants will be withdrawn from the study, and no further data will be collected if they meet the criteria, as shown in Table 2.

**Table 2 Tab2:** The withdrawal criteria for the study

Withdrawal criteria
1. Cancelling planned immunotherapy before the treatment.
2. Patients who break the study protocol (deliberately offering inaccurate PRO data).
3. Patients who demand an immediate withdraw from the research.
4. Severe complications interfering with PRO data collection.
5. Other conditions that require withdrawal as assessed by the investigator.

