### Outcome measures

#### Primary outcome

The primary outcome of this study is the symptom burden in patients with lung cancer during the first-line combination immunotherapy course. It will be assessed using the MDASI-LC and symptomatic irAEs scale directly from patient self-reports. MDASI-LC [17], the lung cancer-specific PRO measurement, will be translated into simplified Chinese to collect longitudinal symptom data once before treatment (typically within 3 days before treatment) and weekly throughout the treatment and till 1 month after treatment completion. It comprises 16 symptoms (pain, fatigue, nausea, disturbed sleep, distress, short breath, remember things, lack of appetite, drowsy, dry mouth, sad, vomiting, numbness, cough, constipation, and sore throat) and six functional items (activity, mood, work, relations, walking, and enjoy life). Each item uses a 0-10-point scale, with 0 representing “symptom has not been present or no functional impairment” and 10 representing “the most severe symptoms or functional impairment”. In addition, the symptomatic irAE scale is a subgroup of symptomatic irAE items from the Patient Reported Outcomes version of the Common Terminology Criteria for Adverse Events library [18, 19], which provides a valid and reliable assessment of symptomatic toxic effects from the patient’s perspective, and is encouraged for use in oncology trials to enhance the accuracy of adverse event reporting [19]. The scale consisting of 15 items (bellyache, diarrhea, bloated pain, night sweats, headache, rash, chills and fever, pruritus, pectoralgia, hemoptysis, abdominal, early satiety, taste change, smell change, and palpitation) will be translated into Chinese to collect the severity score of irAEs. Like the MDASI-LC, it also uses a 0–10 scale, where 0 represents “symptom has not been present or no functional impairment” and 10 represents “the most severe symptoms or functional impairment”.

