### Quality control

The present study will be implemented by and receive guidance and supervision from a multidisciplinary team comprising the principal investigator, subcenter principal, clinicians, clinical research methodologists, statisticians, research assistants, data managers, data monitors, and data quality control staff. A SOP will be proposed as an important reference to guarantee the quality of entered data, and all participants involved in the study are bound to receive SOP training prior to starting the recruitment of patients. As for subcenters, investigators will receive regular online guidance and telephone supervision, and on-site monitoring from the principal investigator to control the quality of data entry. When entering the data, the REDCap system can immediately execute automatic logical verification to correct the faults in this process. In addition, there will be regular and non-scheduled data checking during the patient recruitment process, and all data will receive a final verification for completeness and accuracy after data entry.

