### Data confidentiality

To protect data privacy, participants involved in the study will get a unique study ID (consisting of two sets of numbers) for personal identifying information that is not irrelevant to the assessment. All data (including all personal data) will be stored in the REDCap of Sichuan Cancer Hospital, and all investigators will have access to them.

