### Data analysis

Participants who meet the withdrawal criteria for the study will not be included in the final analysis. For the study results, descriptive analysis will be undertaken by using mean ± SD or median with interquartile range (IQR) for continuous variables, and absolute number (n) and proportion (%) for categorical variables. First, we will use descriptive statistics to describe the severity and time trend of symptom burden and functional interference in patients treated with combination immunotherapy. Symptom trajectories will be depicted with line graphs describing the severity score of patients reporting symptoms from pre-treatment to complete the whole treatment course for 1 month. Furthermore, the association between symptom and clinical outcomes will be examined. Specifically, the symptoms will be categorized based on the severity, and the difference in clinical outcomes (including incidence rate of grade 3–4 immunotoxicity, the completion rate of six cycles of immunotherapy, the timeliness of treatment, complication rate, unplanned clinic rate, OS and PFS) will be assessed. We will use R v.4.2.0 to perform the statistical analysis, and differences will be considered statistically significant if the two-tailed *p*-values are < 0.05.

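### Suspected dishonest self-reporting removes the whole patient from the analysis, and nothing shown keeps that judgement separate from the clinical outcomes

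*Protocol article*

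**What the plan says.** The protocol article fixes two rules that act together.

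- Withdrawal criteria, Table 2, criterion 2 covers "Patients who break the study protocol (deliberately offering inaccurate PRO data"). The text above the table gives the consequence: "Participants will be withdrawn from the study, and no further data will be collected if they meet the criteria".
- Data analysis, opening sentence: "Participants who meet the withdrawal criteria for the study will not be included in the final analysis".

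Three other places bear on how the judgement could be made.

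- Background describes a PRO as information taken "directly from the patients’ perspective without interpretation from others", and Primary outcome relies on that source: "It will be assessed using the MDASI-LC and symptomatic irAEs scale directly from patient self-reports".
- Data confidentiality states that all data are held in one REDCap database and that "all investigators will have access to them".
- Data analysis plans to group symptoms by severity and compare clinical outcomes between the groups: grade 3–4 immunotoxicity, completion of six cycles, timeliness, complications, unplanned clinic visits, OS and PFS. Two-tailed p < 0.05 counts as significant.

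The article does not state how deliberate inaccuracy is recognised, who decides, or whether the decision is made without sight of outcomes.

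**The concern.** The unit of removal does not match the unit of the problem. An unreliable questionnaire is a defect of one report. Under the two rules it costs the patient's other weekly reports and all clinical outcomes, which come from records or follow-up and are not in doubt.

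The judgement is also delicate. A 0–10 self-rating has no external reference value, and intent has even less of one. One ground on which suspicion might arise is that the scores do not fit the patient's course: high scores with an easy course, or low scores with a bad one. Nothing shown excludes that ground. Removing such patients would select on agreement between symptom score and clinical outcome, which is the relation that the association analyses test. Symptoms would then look more predictive than they are.

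**Working it through.** **The rules side by side.** Criterion 2 withdraws the patient; the Data analysis sentence excludes anyone withdrawn. Together they give whole-patient exclusion. That much is stated in the article and is not inferred.

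**The plan's own figure.** The article gives no number of removals under criterion 2. The only relevant figure is the sample size, needed here to set the size of the analysis set. With the inputs in Sample size calculation (means 1.6 and 1.0, SDs 1.1 and 0.7, 30% with adverse events, two-sided 5%, 90% power):

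N = (1.960 + 1.282)² × (1.1²/0.3 + 0.7²/0.7) / 0.6² = 10.51 × 4.733 / 0.36 = 138.2

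Allowing for 20% dropout gives 138.2/0.8 = 173 or 138.2 × 1.2 = 166. Both are close to the stated 168, which is not in dispute. Taking 20% off 168 leaves 168 × 0.8 = 134 patients.

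**What removal by mismatch would do.** Assumptions, none of them from the article except 134 (derived above) and 30% (borrowed from the adverse event rate):

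- 134 patients, right-skewed (gamma) symptom scores, and a binary outcome in 30% that is independent of the score, so the true odds ratio is 1.0.
- The k patients with the greatest rank discordance (high score without the event, low score with it) are removed. This is the worst case for a given k.
- 4,000 simulated trials per scenario, two-sided 5% tests.

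| Removed | High/low split at the median, chi-square: rejects | Average odds ratio | Mean comparison, Welch t-test: rejects |
|---|---|---|---|
| 0 | 5.2% | 1.00 | 5.2% |
| 2 | 5.6% | 1.05 | 6.5% |
| 4 | 6.5% | 1.12 | 10.5% |
| 7 | 9.8% | 1.24 | 21.0% |

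If about half of the 7 removals are unrelated to the outcome, the split rejects in about 6% and the mean comparison in about 9% to 10%, with an odds ratio of about 1.11. If all 7 are unrelated to it, the error stays at about 5%. Repeat runs gave the same picture within simulation error.

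**Which column applies.** The plan groups symptoms by severity before comparing outcomes, so the split column is the nearer match. The mean comparison corresponds to the test used for the sample size.

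**The case against.** Much of the case on the other side stands.

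- *No passage says that scores are compared with the clinical course.* Correct. A reader might infer that investigators will drop patients whose scores disagree with their course, so that the association will be inflated. The documents do not support that. The criterion requires deliberate inaccuracy, and mismatch alone does not meet its wording. Applied without regard to outcomes, the rule would cost precision or shift results in an unknown direction.
- *The criterion could rest on outcome-blind signs.* Also correct. Duplicate submissions or uniform answers are visible without knowing any outcome, so it is too strong to say that no standard could exist.
- *The quality check is not a second chance to remove patients.* A reader might take the statement that "all data will receive a final verification for completeness and accuracy after data entry" as a check on truthfulness once outcomes are known. In context it follows REDCap logic checks and concerns entered data. Withdrawal is described as stopping further collection, so it happens during the study, when completion of six cycles, PFS and OS are often not yet known, although toxicity may be.
- *An SOP or full protocol may define the judgement.* It may, and the absence of a definition from an article is not the point here. The article itself states an intent-based criterion and whole-patient exclusion. A definition elsewhere would not restore the valid reports and outcomes.
- *Criterion 5, the investigator's general discretion, would allow the same removal.* True, so deleting criterion 2 alone would not be enough.

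**Conclusion.** The point holds as a flaw in a stated rule, with a conditional effect. Suspected dishonesty in some reports excludes the whole patient, and nothing shown requires the judgement to be blind to outcomes. Inflation of the symptom-outcome association is a risk and not an established direction.

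Its size is modest for the kind of comparison planned. In the worst case, the 5% error becomes about 6% with 2 to 4 removals and about 10% with 7, and stays at about 6% if half of the 7 are random. The larger figures, about 11% with 4 and 21% with 7, belong to a comparison of mean scores and would overstate the effect on severity groups. All of this rests on an assumed number of removals and an assumed removal rule.

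The inflation risk concerns the associations with secondary and exploratory outcomes. The primary outcome, symptom burden, is analysed descriptively; there the rule's certain cost is the valid reports lost from any patient excluded.

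**What to change.** 1. Stop using suspected inaccuracy as a reason to exclude a patient from the analysis, whether under criterion 2 or through criterion 5, and change the exclusion sentence in Data analysis to match.
2. Flag suspect questionnaires by response-pattern rules fixed before analysis and applied without sight of clinical outcomes. Examples are the same non-zero answer to all 37 items (16 + 6 from the MDASI-LC and 15 from the irAE scale) or duplicate submissions. Completion time can be used only if it is recorded, which the article does not say.
3. Set only flagged reports to missing. Keep the patient's other reports and all clinical outcomes.
4. Report how many questionnaires were flagged and why, and repeat the main results with flagged reports included.

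The cost is small: an edit to Table 2, a sentence in Data analysis and a simple check on the electronic questionnaire data. The downside is that unreliable reports which the rules miss stay in and add some noise.

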### Sample size calculation

This study will mainly focus on establishing temporal trends in the symptom burden of patients with advanced lung cancer receiving combination immunotherapy and symptom burden in patients with adverse events should be distinguished from that in patients without adverse events. It is estimated that adverse events develop in 30% of patients receiving immunotherapy, and our preliminary research data showed that the symptom score of the patients with adverse events was 1.6 ± 1.1, and the symptom score of the patients without adverse events was 1.0 ± 0.7. According to the t-test of the two groups’ mean and 20% of dropout rate, with a type I error rate of 5% and a power of 90%, using two-sided test, the final sample size is approximately 168 cases.

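### On the printed inputs, 168 enrolled with 20% dropout gives about 88–89% power, slightly below the stated 90%

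*Protocol article*

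**What the plan says.** The section Sample size calculation of the protocol article bases the total on a two-group t-test comparing patients with and without adverse events. Its inputs are:

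- Group split: "adverse events develop in 30% of patients receiving immunotherapy".
- Pilot scores: "the symptom score of the patients with adverse events was 1.6 ± 1.1" and "the symptom score of the patients without adverse events was 1.0 ± 0.7".
- Loss: "20% of dropout rate".
- Error rates and result: "with a type I error rate of 5% and a power of 90%, using two-sided test, the final sample size is approximately 168 cases".

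The Abstract repeats the total as the recruitment target: "We will prospectively recruit 168 eligible patients from 14 hospitals in China". The section Data analysis leaves anyone who meets the withdrawal criteria out of the final analysis, and the section Withdrawal criteria stops their data collection. The article prints neither the number of evaluable patients before the dropout allowance nor the way the allowance was applied.

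**The concern.** A dropout allowance should leave the required number of evaluable patients after the loss. If a fraction d is lost, the number to enrol is the evaluable number divided by (1 − d). Multiplying by (1 + d) gives too few, because the loss applies to everyone enrolled and not only to the number needed at the end. The stated total matches the multiplied version exactly. If dropouts contribute nothing to the comparison, as the exclusion rule implies, the section's 90% power and 20% dropout cannot both hold at 168 on the figures it prints. At stake is the accuracy of a stated design property, not the viability of the study.

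**Working it through.** **Inputs**, all from Sample size calculation: difference 1.6 − 1.0 = 0.6; SDs 1.1 (with adverse events) and 0.7 (without); split 30:70; two-sided 5%; power 90%; dropout 20%.

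**Step 1: evaluable patients needed.** Use the normal approximation with separate variances and n2 = (7/3) n1:

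n1 = (1.960 + 1.282)² × (1.1² + 0.7² × 3/7) / 0.6² = 10.507 × 1.42 / 0.36 = 41.4, rounded up to 42.

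n2 = 42 × 7/3 = 98. Total 42 + 98 = **140**. The unrounded total is 10.507 × (1.21/0.3 + 0.49/0.7) / 0.36 = 138.2.

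**Step 2: reproduce the stated total.**

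- 140 × 1.2 = **168**, the article's figure exactly.
- 140 / 0.8 = **175**, which is 7 more. From the unrounded figure, 138.2 / 0.8 = 173.

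Other routes were tried: a common SD (several choices), a 1:1 split, a one-sided test and 80% power. None gives 168 exactly while respecting the stated two-sided test, both SDs, 90% power and a dropout allowance. One-sided testing with a common SD of 1.1 also gives 140 and then 168, but it contradicts the printed two-sided test and the two separate SDs.

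**Step 3: power after the stated dropout.** 168 × 0.8 = 134.4, so about 134 evaluable, or about 40 + 94 at a 30:70 split.

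- Standard error: √(1.21/40 + 0.49/94) = 0.1883.
- Standardised difference: 0.6 / 0.1883 = 3.186.
- Normal approximation: Φ(3.186 − 1.960) = Φ(1.226) = **89.0%**.
- Unequal-variance (Welch) t-test, noncentral t with about 53 degrees of freedom: **87.9%**.

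**Step 4: the dropout that 168 can absorb.** (168 − 140) / 168 = 28/168 = **16.7%**. At 42 + 98 the power is 90.4% by the normal approximation and 89.4% by Welch.

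**Step 5: separate the two sources.** On the formula that reproduces 168, the dropout step costs about 1 point of power and 7 patients. The second point comes from replacing the normal approximation with a t-test. On that basis 43 + 100 = 143 evaluable patients are needed for 90%, and 143 / 0.8 = 178.75, so 179 enrolled.

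**The case against.** The strongest objection is that the mechanism is inferred. Neither 140 nor the multiplication by 1.2 is printed, the total is called approximate, and the exact match depends on rounding up to a whole-number 3:7 split (138.2 × 1.2 = 165.8). The pilot values are printed to one decimal. Unrounded values that would print the same way can give about 168 with the correct division by 0.8. A difference of 0.608 gives 168.2, and SDs of 1.085 and 0.69 give 168.0. This stands: a reader might infer that the total is proven to come from a wrong inflation formula, but the article does not establish that. Multiplication is only the simplest reading of the printed figures.

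The objection about size also stands. The shortfall is about 1 point on the formula that reproduces 168. Uncertainty in the inputs matters far more: a difference of 0.55 instead of 0.6 would require about 206 enrolled, and 0.65 about 147. The study is an observational cohort whose trajectories are analysed descriptively, and Data analysis does not list this t-test among its comparisons. A reader might infer a material loss of power or a need to recruit more patients, and the figures support neither.

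A reader might also note that a pooled-variance t-test would have an inflated type I error here, because the larger SD is in the smaller group. The article prints separate SDs and does not specify a pooled test, so this is no charge against it. Naming the t-test variant is detail that an analysis plan may hold.

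What does not fall is the mismatch itself. However 168 was reached, the printed inputs with a 20% loss give less than 90% power.

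**Conclusion.** The point holds as a minor correction. On the inputs as printed, 168 enrolled with 20% lost leaves about 134 evaluable patients and about 89% power (normal approximation) or about 88% (unequal-variance t-test), against the stated 90%. The total that keeps both stated properties is about 175 on the formula that reproduces the article's figure.

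This rests on three assumptions: the printed means and SDs are taken at face value; losses fall evenly on the two groups, so the 30:70 split is kept; and dropouts contribute nothing to the comparison, in line with the exclusion rule in Data analysis. The size of the overstatement does not depend on how the authors reached 168. The explanation through 140 × 1.2 does, and should be presented as likely, not as established.

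**What to change.** Keep 168, print the evaluable number behind it (140 if that is what was used), and replace the power sentence with one of two statements:

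- with 168 enrolled and 20% dropout, about 134 evaluable patients give about 88–89% power; or
- 168 enrolled allows about 16.7% dropout, leaving 140 evaluable patients and about 90% power.

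If the total was in fact derived from unrounded pilot values and division by 0.8, printing those values to one more decimal would settle the matter instead.

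The cost is one sentence and, in the first two cases, a slightly less favourable power or dropout figure. No extra enrolment or design change is needed.
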